### Plans for assessment and data collection

4.1

Potential participants will be screened by trained investigators to ensure compliance with the inclusion and exclusion criteria. Screening will include a review of medical records and current radiotherapy or chemoradiotherapy details to confirm the diagnosis of head and neck cancer. Eligible participants will be informed about the study objectives, procedures, risks, and benefits, and written informed consent will be obtained prior to enrolment. All screening details will be documented in the screening form and case record form (CRF), with reasons recorded for screen failures. Participants meeting eligibility criteria will proceed to baseline assessments, randomisation, and initiation of the allocated intervention.

At the screening or baseline visit, detailed clinical and drug histories will be recorded. Clinical examination will then be performed to assess the oral mucositis severity using the RTOG and WHO Oral Mucositis Scales during baseline visit. Baseline laboratory investigations, including complete blood count (CBC), liver function test (LFT), and renal function test (RFT), will be performed. Participants will then be randomised, and study medications will be dispensed as per group allocation. Follow-up assessments will be conducted weekly by trained assessors throughout the course of radiotherapy, with telephonic follow-up continued up to six weeks post-radiotherapy. The severity of oral mucositis will be assessed using RTOG and WHO oral mucositis scales, pain intensity will be measured using a 10-point VAS, and analgesic use will be documented according to WHO three-step analgesic ladder. Details of the grading criteria for all these four scales are presented in Table 3. However, in certain clinical situations, analgesics, particularly opioids, may be prescribed for cancer-related pain rather than for RIOM. In such cases, the indication for analgesic use may not directly reflect RIOM severity. To address this, all analgesic usage will be documented along with the primary indication, and cases where analgesics are administered for non-RIOM-related pain, will be clearly specified with appropriate justification. All assessors and physicians involved in outcome evaluation will be trained in advance regarding grading scales and assessment procedures.

**Table 3 T3:** Assessment scales used for outcome evaluation.

Assessment Tool	Grade/Scale	Grading Description

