RTOG Oral Mucositis Scale	Grade 0	No change
	Grade 1	Irritation/ Mild pain not requiring analgesics
	Grade 2	Patchy mucositis with inflammatory serosanguinous discharge/ moderate pain requiring analgesics
	Grade 3	Confluent fibrinous mucositis/ severe pain requiring narcotic analgesics
	Grade 4	Ulceration, haemorrhage, or necrosis
WHO Oral Mucositis Scale	Grade 0	No oral mucositis
	Grade 1	Erythema and soreness
	Grade 2	Ulcers present & able to eat solid food
	Grade 3	Ulcers present& requires liquid diet due to mucositis
	Grade 4	Ulcers present; alimentation not possible due to mucositis
VAS for Oral Cavity Pain	0	No pain
	1–3	Mild pain
	4–6	Moderate pain
	7–10	Severe pain
WHO Three-Step Analgesic Ladder	Step 1	Mild pain; Non-opioid analgesics (paracetamol, NSAIDs) ± adjuvants
	Step 2	Mild to moderate pain; Weak opioids (e.g., codeine, tramadol) ± non-opioids and/or adjuvants
	Step 3	Moderate to severe pain; Strong opioids (e.g., morphine, fentanyl, oxycodone) ± non-opioids and/or adjuvants

To evaluate treatment response over time, the percentage distribution of grades/scores obtained from the four above mentioned scales will be assessed separately for each study arm at weekly intervals during study period. These assessments will help compare the severity of mucositis, recovery patterns, pain levels, and analgesic requirements between the two groups over the course of treatment and follow-up. Certain practical limitations may arise while applying the WHO oral mucositis scale in specific clinical situations. For example, some patients may already be receiving nutrition through a nasogastric (NG) tube due to tumour-related obstruction, poor nutritional status, or severe RIOM. In such cases, oral intake is restricted to liquids irrespective of the actual severity of mucositis, which could result in overestimation of the grade, such as categorizing the condition as Grade 3 despite the absence of corresponding clinical findings. To avoid such misclassification, these cases will be recorded as “Not Applicable” for WHO grading, along with proper justification in the study records.

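### The rule that sets WHO mucositis grades to not applicable during tube feeding also covers tubes placed because of severe RIOM, so the worst visits go missing from the WHO outcome

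*Protocol article*

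**What the plan says.** All of this stands in the protocol article.

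- **The rule (Section 4.1, text after Table 3).** It starts from the situation that "some patients may already be receiving nutrition through a nasogastric (NG) tube due to tumour-related obstruction, poor nutritional status, or severe RIOM". It treats liquid intake in all three situations as uninformative about mucositis: "poor nutritional status, or severe RIOM. In such cases, oral intake is restricted to liquids irrespective of the actual severity of mucositis". The risk it names is over-grading, "such as categorizing the condition as Grade 3 despite the absence of corresponding clinical findings". The remedy covers the whole group: "To avoid such misclassification, these cases will be recorded as" not applicable, with a written justification. It does not separate the causes.
- **The scale (Table 3).** WHO grade 3 needs ulcers in a patient who "requires liquid diet due to mucositis". WHO grade 4 reads "Ulcers present; alimentation not possible due to mucositis".
- **Where WHO grades are used.** Section 2.5 makes the WHO scale a secondary outcome and RTOG grade 3 or higher the primary outcome. Section 4.5 names both scales in the primary outcome analysis, with a cut at grade 2 or higher, and adds an analysis of weekly grade distributions.
- **Discussion (Section 7).** It again lists severe RIOM among the causes of tube feeding that may inflate the grade. It says only that such factors will be documented and considered in the analysis.
- **Related wording on RTOG.** Table 3 words grade 3 as "Confluent fibrinous mucositis/ severe pain requiring narcotic analgesics", while Section 4.1 notes that "analgesics, particularly opioids, may be prescribed for cancer-related pain rather than for RIOM".

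**The concern.** For a tube placed because of tumour obstruction or poor nutrition, the rule is sensible: diet then says little about the mucosa. For a tube placed because of severe RIOM, the reasoning contradicts the scale. The change in intake is caused by mucositis, which is what grades 3 and 4 record, so there is no over-grading to prevent.

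Coding these visits as not applicable turns the worst mucositis into missing data, and whether a value is missing depends on the value itself. The weekly WHO distributions would look milder in both arms. Any between-arm comparison that leaves these participants out would rest on a group selected by outcome. Because the tube is placed after randomisation, the selection can differ between arms.

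**Working it through.** **No figure in the plan to reproduce.** The point concerns a recording rule. The text comparison comes first, then an illustration of size.

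**1. Text against scale.**

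| Reason for tube | Is intake unrelated to mucositis? | Does the over-grading rationale apply? |
|---|---|---|
| Tumour obstruction | Yes | Yes |
| Poor nutritional status | Yes, unless mucositis caused it | Yes, with that exception |
| Severe RIOM | No, mucositis is the cause | No: Table 3 grades 3 and 4 describe this state |

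**2. When such tubes arise.** Section 2.4.1 starts treatment the day before radiotherapy or on the same day, and Section 2.3.2 excludes re-irradiation. Tube feeding for radiation-induced mucositis therefore begins after randomisation. Section 2.5 also collects the need for a tube as an exploratory outcome.

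**3. Formula.** Let p be the true proportion ever severe on the WHO scale, and k the share of severe participants who are tube-fed for RIOM and have no severe grade recorded earlier. If they leave the analysis:

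observed rate = p(1 − k) / (1 − pk)

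observed odds = (1 − k) × p/(1 − p)

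**4. Equal shares in both arms.** Assumed: p = 40% (SOC) and 25% (Siddha + SOC), cut at grade 3 or higher. Neither the rates nor this cut for WHO is set in the plan. The true difference is 15.0 points and the true relative reduction is 1 − 25/40 = 37.5%.

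At k = 0.5:
- SOC: 0.40 × 0.5 / (1 − 0.20) = 0.20/0.80 = 25.0%
- Siddha + SOC: 0.25 × 0.5 / (1 − 0.125) = 0.125/0.875 = 14.3%

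| k | SOC | Siddha + SOC | Difference (points) | Relative reduction |
|---|---|---|---|---|
| 0 (true) | 40.0% | 25.0% | 15.0 | 37.5% |
| 0.10 | 37.5% | 23.1% | 14.4 | 38.5% |
| 0.25 | 33.3% | 20.0% | 13.3 | 40.0% |
| 0.50 | 25.0% | 14.3% | 10.7 | 42.9% |
| 0.75 | 14.3% | 7.7% | 6.6 | 46.2% |

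The odds ratio stays at (0.40/0.60)/(0.25/0.75) = 2.0 throughout, because the factor (1 − k) cancels. The same loss therefore shrinks the absolute difference, enlarges the relative reduction and leaves the odds ratio alone. It also costs participants: at k = 0.5, 80 per arm becomes 80 × 0.80 = 64 and 80 × 0.875 = 70. Power for this comparison (two-sided 5%, before any dropout) goes from about 53% to about 35%.

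**5. Unequal shares.** Take the 43.6% severe rate under benzydamine quoted in Section 2.7, in both arms, so there is no true effect. With k = 0.50 under SOC and 0.25 under Siddha + SOC:
- SOC: 0.218/0.782 = 27.9%
- Siddha + SOC: 0.327/0.891 = 36.7%

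This is a spurious 8.8 points against Siddha. With the shares swapped it is 8.8 points in its favour. For a true 43.6% versus 28.6% (15.0 points), the same two imbalances give 4.8 and 20.0 points.

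**6. The plan's stated effect.** A 15% relative reduction from 43.6% is 0.85 × 43.6 = 37.1%, a difference of 6.5 points. At k = 0.5 in both arms it becomes 5.1 points.

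**The case against.** **Not applicable is a code for a visit, not an exclusion.** This stands. WHO is graded weekly, and a grade 3 recorded before the tube could still count in an ever-severe analysis. A reader might infer that the worst participants are deleted from the WHO outcome altogether; the documents do not say so. The figures above are upper-end values for an ever-severe endpoint. With the grade 2 cut of Section 4.5 the loss is probably smaller still, since most people who reach a tube for RIOM will already have a grade 2 on record. Grade 4 and the weekly distributions have no such protection.

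**The primary outcome is RTOG.** This stands for Section 2.5. RTOG does not depend on diet, so the tube rule leaves that outcome intact. Only the wording of Section 4.5 brings WHO grades into the primary analysis.

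**The rule may be meant only for tubes already in place at baseline, or only where clinical findings are absent.** The purpose stated in Section 4.1 gives this some support. But severe RIOM is listed by name, the remedy refers back to the whole list, and the Discussion repeats the grouping. Tubes for severe RIOM can hardly exist at baseline.

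**Detail belongs in the SAP.** Analysis handling may. The recording rule is stated here, recruitment has begun, and a grade that was never assigned is hard to recover later.

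**Opioids and RTOG.** A reader might infer that an opioid given for tumour pain will count as a primary event. The documents do not establish this: the indication is recorded, Section 4.1 says such use may not reflect RIOM severity, and Section 3.4 has assessors unaware of allocation. What is missing is only a sentence that links the recorded indication to RTOG grading.

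**Conclusion.** The concern holds for the WHO scale. As written, the rule sets to not applicable the visits that grades 3 and 4 are meant to capture, and its stated reason is wrong for tubes placed because of RIOM. The result is outcome-dependent missing data in the WHO secondary outcome, in the weekly distributions, and in the primary analysis as Section 4.5 words it.

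It is tempting to conclude that the treatment effect must be diluted. That does not follow. With equal tube-fed shares the absolute difference falls (15.0 to 10.7 points at half tube-fed) while the relative reduction, which is closer to how Section 2.5 words the WHO outcome, rises (37.5% to 42.9%). With unequal shares the error can go either way and can appear with no true effect (8.8 points in the example).

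The sizes rest on assumed severe rates, an assumed cut at grade 3, an assumed tube-fed share, no earlier severe grade on record, and removal of the participant from the comparison. The contradiction in the text rests on none of these. The RTOG and opioid wording is a secondary, unquantified clarification.

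**What to change.** In Section 4.1, split the rule by the recorded reason for the tube, and align the Discussion:

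- **RIOM is the reason:** assign the WHO grade per Table 3 and count the participant as severe. The guidance should say when grade 3 and when grade 4 applies.
- **Another cause:** keep not applicable. Grading these visits on mucosal signs alone would not work, because WHO grades 2 to 4 all require ulcers and differ only by diet.
- **Both cases:** retain every WHO grade recorded before the tube. State how visits coded not applicable enter the analysis, with a sensitivity analysis that varies their handling.
- **Secondary:** state that an opioid documented as given for non-RIOM pain does not by itself make an RTOG grade 3.

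The cost is CRF guidance and a few lines of protocol and SAP wording. The reason for the tube and the analgesic indication are already to be recorded, so no new data are needed, and visits already coded can be reviewed against the written justification. The small downside is that the assessor must attribute the cause of the tube, which the required justification already asks for. The change concerns outcome recording only, not patient care.

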### Plans to promote participant retention & complete follow-up

4.2

Participant retention will be promoted through regular in-patient engagement during the radiotherapy admission period, enabling close follow-up, supervision of interventions, and minimising participant burden. During the post-radiotherapy period, follow-up will be ensured through scheduled telephonic contacts. Participants and caregivers will receive counselling on the importance of adherence and follow-up, and family caregivers will be trained during radiotherapy to support intervention use after discharge. Reminder calls will be made prior to scheduled visits, and contact details will be verified at enrolment. In the event of missed visits, study staff will attempt prompt telephonic follow-up to collect outcome data wherever feasible, thereby minimising loss to follow-up.

### Data management

4.3

All study-specific data will be recorded in standardised CRFs. Source documents, including medical records and laboratory reports, will be maintained to allow verification of recorded data. Investigators will document all required participant information in the CRFs, with appropriate justification for any missing data. Data recorded in the CRFs will be routinely cross-verified against source documents, and any discrepancies will be addressed and resolved through data clarification. Treatment details, follow-up information, and scheduled visit dates during post-RT period will be documented in a patient diary. Protocol deviations and the use of concomitant or rescue medications, if any, will also be recorded in the CRFs and reviewed by the investigators at each visit.

Participants who discontinue or deviate from the intervention protocol will continue to be followed, and their data will be included in the final analysis in accordance with the *intention-to-treat* principle. To support participant retention and ensure complete follow-up, regular telephonic communication will be maintained.

#### Quality assurance

4.3.1

The Principal Investigator will ensure that all data entered in CRFs are accurate, complete, legible, and recorded in a timely manner. To ensure data accuracy, double data entry will be performed for a sub-sample of participants. The data management team will routinely review the database to identify missing values and discrepancies, and CRF entries will be cross-verified against source documents. Participant-specific records will be periodically reviewed to ensure compliance with data recording and documentation standards. Any identified issues will be communicated to the study team, and corrective feedback will be provided to facilitate continuous improvement in data quality.

### Plans for collection, laboratory evaluation and storage of biological specimens for genetic or molecular analysis in this trial/future use

4.4

No biological specimens will be collected, processed, stored, or used for genetic or molecular analysis as part of this trial or for future research. All laboratory investigations required for clinical assessment, including blood tests, will be performed as part of routine SOC at Regional Cancer Centre and will not involve additional sample collection by the study team.

### Statistical methods

4.5

Baseline demographic and clinical characteristics of the participants will be summarised using descriptive statistical methods. Categorical data will be presented as frequencies and percentages, whereas continuous data will be expressed either as mean ± standard deviation or as median with interquartile range, based on the distribution of the data.

The primary outcome of the study, namely the severity of oral mucositis assessed using RTOG and WHO oral mucositis scales, will be analysed by comparing the proportion of participants who develop grade ≥2 mucositis in the two study groups. Depending on the suitability of the data, either the chi-square test or Fisher's exact test will be used for comparison. In addition, weekly mucositis grade distributions will be analysed to observe changes in severity, recovery patterns, and overall trends during treatment and follow-up.

For secondary outcomes, pain intensity measured using VAS will be compared between the groups at each assessment point using either the independent samples t-test or the Mann–Whitney U test, based on the data distribution. Analgesic use, categorised according to WHO three-step analgesic ladder, will be analysed as categorical data and compared between groups using the chi-square test or Fisher's exact test. Rescue medication use will be analyzed as a secondary outcome to compare overall analgesic requirements between the study groups. Laboratory investigations will be summarised descriptively and assessed for safety through appropriate within-group and between-group analyses.

The distribution of continuous variables will be checked using histograms to determine normality. Depending on the nature of the data, either parametric or non-parametric statistical methods will be applied for between-group comparisons. Subgroup analyses based on cancer treatment modalities will also be carried out to explore whether the treatment effects remain consistent across clinically relevant subgroups. However, these analyses will be considered exploratory in nature.

Efficacy analysis will follow a modified *intention-to-treat* approach, including all randomised participants who have undergone at least one post-baseline assessment. Safety analysis will be performed using the per-protocol population. A two-sided *p* value of ≤0.05 will be considered statistically significant. All statistical analyses will be carried out by a statistician using the Statistical Package for the Social Sciences (SPSS) software.

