### Background and rationale

1.1

Head and neck cancer arises from the epithelial lining of the upper aerodigestive tract and represents the seventh most common malignancy worldwide (1). Radiotherapy, either alone or in combination with concurrent chemotherapy, remains a cornerstone in the management of these malignancies (2). However, these treatment strategies are commonly associated with wide range of oral complications, including oral mucositis, secondary infections, xerostomia, dysgeusia, pain and an increased risk of dental and periodontal diseases. These complications impair essential activities like eating, swallowing, speaking and thereby reducing quality of life of patients. In severe cases, they may lead to treatment interruptions, infections and compromised oncological outcomes (3, 4).

Among the complications, oral mucositis (OM) is one of the most dose limiting toxicity of cancer treatment and it is featured by inflammation and ulceration of oral mucosa, typically developing 5–7 days after the initiation of chemo and radiotherapy. Approximately 40% of head and neck cancer patients receiving chemotherapy alone develop OM, whereas 90%–100% patients receiving concurrent chemo-radiotherapy (5). Evidence from Indian clinical settings indicated that radiation-induced oral mucositis (RIOM) usually appears after a cumulative radiation dose of approximately 20Gy, becomes more widespread at around 30Gy, and reaches peak severity with Grade 3 reactions at cumulative doses of 66 – 70Gy (6).

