### Objectives

1.3

The primary objective of this study is to evaluate the proportionate reduction in the occurrence of severe RIOM, as assessed using RTOG grading scale, among participants receiving a Siddha regimen as an adjunct to standard care compared with those receiving standard care alone, assessed during radiotherapy and at six weeks post-radiotherapy.

The secondary objectives are to assess the proportionate reduction in the severity of radiation-induced oral mucositis using WHO oral mucositis scale at the same time points; to compare oral cavity pain intensity between the study groups using VAS, assessed weekly throughout the study period; to evaluate changes in analgesic usage, including escalation or de-escalation according to the WHO Three-Step Analgesic Ladder, on a weekly basis during the study period; to estimate and compare the proportion of adverse reactions between the study groups; and to evaluate differences in the frequency and duration of treatment interruptions attributable to oral mucositis between the study groups.

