### Outcomes

2.5

The primary outcome of the study is the severity of RIOM, assessed using RTOG grading scale. This will be measured as the proportion of participants who develop severe oral mucositis (RTOG grade ≥ 3) at any time during radiotherapy and up to six weeks following completion of radiotherapy, compared between the two study arms. The primary outcome will be assessed from randomisation until the last day of study medication use.

The secondary outcomes include oral mucositis severity assessed using WHO oral mucositis scale, measured as the proportionate reduction in the occurrence and severity of mucositis during radiotherapy and up to six weeks post-radiotherapy. Oral cavity pain, evaluated using VAS as the proportion of participants achieving a minimum two-point reduction in pain intensity and analgesic usage, assessed as the percentage of participants requiring analgesics categorised according to WHO three-step analgesic ladder. Safety outcomes will be evaluated by documenting the number of adverse events reported in each study group. Treatment interruption will be assessed as the proportion of participants experiencing one or more radiotherapy interruptions due to severe RIOM and the total number of days of missed radiotherapy. In addition, body weight changes during radiotherapy, requirement for nasogastric tube feeding, and interruptions in oral intake will be documented as exploratory indicators of nutritional impact. All secondary outcomes, except treatment interruption, will be assessed from randomisation until the last day of study medication use, while treatment interruption will be evaluated until the completion of radiotherapy.

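### The only named between-arm test for WHO mucositis severity is a grade ≥2 cut that merges grades 2, 3 and 4; an ordinal comparison is a cheap, minor improvement to this secondary outcome

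*Protocol article*

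**What the plan says.** Section 1.3 of the protocol article (Objectives) sets a secondary objective to "assess the proportionate reduction in the severity of radiation-induced oral mucositis using WHO oral mucositis scale at the same time points". Section 2.5 (Outcomes) repeats the secondary role and describes the outcome as "oral mucositis severity assessed using WHO oral mucositis scale, measured as the proportionate reduction in the occurrence and severity of mucositis".

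Section 4.5 (Statistical methods) puts both scales under one label, "The primary outcome of the study, namely the severity of oral mucositis assessed using RTOG and WHO oral mucositis scales", and states that this "will be analysed by comparing the proportion of participants who develop grade ≥2 mucositis in the two study groups". For that proportion, "either the chi-square test or Fisher's exact test will be used for comparison". It then adds that "weekly mucositis grade distributions will be analysed to observe changes in severity, recovery patterns, and overall trends during treatment and follow-up". Section 4.1 says that weekly grade percentages are worked out separately for each arm and are meant to help compare the arms. Neither section names a between-arm test, an effect measure or a per-participant summary for these distributions.

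Table 3 separates the upper WHO grades by diet: solid food is possible at grade 2, only liquids at grade 3, and no alimentation at grade 4. Section 4.1 also provides that the WHO grade is recorded as 'Not Applicable' where nasogastric feeding would distort it.

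**The concern.** The outcome is severity on a five-level ordered scale, but the one named comparison asks only whether a participant ever reached grade 2. A participant whose worst grade is 2 counts the same as one whose worst grade is 4. The trial hopes to see fewer severe cases, and that benefit lies exactly where this cut cannot see it. If the regimen moved participants from grades 3–4 to grade 2, the WHO comparison could be read as showing no effect on severity.

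The loss grows as the control rate of grade ≥2 approaches 100%. Section 1.1 gives a reason to think the rate may be high: mucositis of any grade occurs in about 40% with chemotherapy alone, "whereas 90%–100% patients receiving concurrent chemo-radiotherapy".

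**Working it through.** **Inputs from the article.** Severe mucositis under benzydamine is 43.6%, the assumed effect is a 15% relative reduction, and there are 64 per arm before dropout (all section 2.7). The significance level is 5% two-sided.

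**The plan's own figure.** The 64 reproduces from the printed formula with πS = 0.436, πT = 0.85 × 0.436 = 0.3706, δ = +0.15 and a one-sided 5% level: (1.645 + 0.842)² × [0.436 × 0.564 + 0.3706 × 0.6294] / (−0.0654 − 0.15)² = 63.8. The stated two-sided level gives 81.1, so 82. That mismatch is a separate matter. Here 64 serves only as the number analysed per arm.

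**Assumptions, because no WHO grade distribution is given.** Control grade ≥3 is 43.6%. This is borrowed from section 2.7, which reports it for severe mucositis without naming a scale. Control grade ≥2 is varied from 75% to 95%.

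**Step 1: shift confined to grades 3–4.** Let grade ≥3 fall from 43.6% to 28.6% and grade 2 rise by the same 15 points. The proportion at grade ≥2 is then equal in the two arms, whatever its level. The cut rejects only at its false-positive rate, about 5%. The equality follows from the definition and needs no grade distribution.

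**Step 2: common odds ratio across all grades.** For the same 15-point fall, OR = (0.286/0.714) / (0.436/0.564) = 0.518. Applying it to grade ≥2, for example at 75%: odds 3 × 0.518 = 1.555, so 60.9%. Power of the cut uses the normal approximation for two proportions. Ordinal power uses the proportional-odds formula Φ(|ln OR| × √V − 1.96), with V = (128/12) × (1 − Σp̄³), where p̄ is the mean of the two arms' grade probabilities.

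| Control ≥2 | Test arm ≥2 | Power, ≥2 cut | Power, ordinal | n per arm for 80%: ≥2 cut | n per arm for 80%: ordinal |
|---|---|---|---|---|---|
| 75% | 60.9% | 40% | 54% | 170 | 118 |
| 85% | 74.6% | 31% | 53% | 233 | 123 |
| 90% | 82.3% | 24% | 51% | 318 | 129 |
| 95% | 90.8% | 15% | 48% | 581 | 138 |

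A ≥3 cut (43.6% against 28.6%) has 42% power and needs 160 per arm.

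Simulation with other control splits of grades 0 to 4 (5/20/31.4/37/6.6%, 3/10/43.4/37/6.6% and 2/4/50.4/38/5.6%, so 75%, 87% and 94% at grade ≥2) gives 18–41% for the cut and 48–53% for the Mann-Whitney test. Over all runs the ranges are about 15–42% and 47–54%.

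**Step 3: power for the Step 1 shift, by simulation.** The ≥2 cut has about 5%, the Mann-Whitney test about 23–36% (a separate set of runs gave 21–34%), and a ≥3 cut 43–46%.

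**Step 4: the protocol's 15% relative reduction.** OR = (0.3706/0.6294) / (0.436/0.564) = 0.762. The ≥2 cut has about 7–11% power and the ordinal test about 13% for control ≥2 rates up to 94%. At 95% they have 5% and 12%. A ≥3 cut has 11%.

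**Step 5: ordinal test against a ≥3 cut.** Under a common odds ratio of 0.52 the ordinal test is ahead by about 4–11 points in simulation (6–12 by the formulas: 48 − 42 to 54 − 42). For the shift confined to grades 3–4 it is behind.

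**The case against.** Most of the loss comes from where the cut lies rather than from cutting at all. Section 4.5 uses grade ≥2, whereas section 2.5 defines the RTOG primary outcome at grade ≥3. If that conflict were settled at ≥3 for both scales, Step 5 shows that little would remain to gain, and a shift confined to grades 3–4 would be better detected by the ≥3 cut. Such a shift also breaks the proportional-odds assumption. This stands, and it is why the point is small and why the fix includes the ≥3 difference.

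A reader might infer that the grades are thrown away altogether. The article does not support that: weekly distributions are analysed and shown per arm, and a move from grade 4 to grade 2 would be visible there. What is missing is a between-arm comparison based on them. One could leave that to an analysis plan, but the ≥2 cut is a stated choice and not an omitted detail.

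A reader might also infer that grade ≥2 is documented to be near its ceiling. It is not. The 90–100% in section 1.1 is any-grade mucositis under concurrent chemoradiotherapy, and the figure of over 90% in section 7 is for high-dose treatment. The trial also enrols radiotherapy-alone and post-operative patients. The point does not need the ceiling: at 75% the ordinal test still gains 54 − 40 = 14 points under a common odds ratio.

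Finally, WHO grades 2 to 4 differ only by diet, and sections 4.1 and 7 warn that tube feeding can inflate the grade. A worst-grade analysis leans on that distinction more than a ≥2 cut does, so the fix must deal with 'Not Applicable' assessments.

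**Conclusion.** The point holds as a minor, inexpensive improvement to a secondary outcome. The only named between-arm test for WHO severity cannot register a move from grades 3–4 to grade 2; that follows from the definition of the cut. The power figures depend on an assumed grade distribution and on 43.6% being transferable to WHO grade ≥3. On those assumptions, an ordinal test improves on the ≥2 cut by about 14 to 33 points at an odds ratio of 0.52 (54 − 40 and 48 − 15).

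Two stronger conclusions are not supported. The ordinal test is not the best choice for every pattern of benefit, since a ≥3 cut does better when the shift stays within grades 3–4 to 2. Nor would the change give the trial adequate power for WHO severity: at 64 per arm the ordinal test reaches only about half, and at the protocol's own 15% relative reduction about 13%. Nothing here argues for changing the RTOG primary outcome. The difference between ≥2 in section 4.5 and ≥3 in section 2.5 has to be reconciled in its own right.

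**What to change.** In section 4.5, take the WHO scale out of the primary-outcome sentence. Compare each participant's worst WHO grade (0–4) during radiotherapy and the six weeks after it, by a Mann-Whitney test or a proportional-odds model, reporting a common odds ratio with 95% CI. Beside it, show the percentage at each grade in each arm and the between-arm difference in the grade ≥3 proportion with 95% CI, because a shift confined to grades 3–4 would break proportional odds.

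State that assessments recorded as 'Not Applicable' do not contribute to the worst grade, and report their number by arm. Section 4.1 lists severe mucositis among the reasons for tube feeding, so an imbalance in these counts would matter for interpretation.

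The cost is a few sentences. WHO grades are already collected weekly (Table 2), and the Mann-Whitney test is already planned for pain. The downside is that a common odds ratio is less direct to read than a proportion, which the percentages by grade and the ≥3 difference offset.
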